#### Population of Analysis

Efficacy and safety studies shall be conducted in the entire clinically evaluable population.

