### Criteria for Discontinuation of Treatment/Intervention

A patient will be withdrawn from the study when the investigator becomes aware that a participant is experiencing a serious or intolerable adverse event that prevents continuation of the drug study.

The patient may also be excluded from the study at the investigator’s request (eg, if the investigator believes that the participant’s health could be compromised by continued treatment with the study drug). Noncompliance is not grounds for discontinuing treatment.

If a patient becomes pregnant during the study treatment period, treatment with the study drug must be discontinued. However, the participant must remain in the study to continue with safety and other study assessments.

Discontinuation may also occur at the participant’s request if they do not wish to continue drug treatment.

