### Statistical Analysis

#### Sample Size Determination

Based on clinical experience, it is estimated that the efficacy of cytisinicline prescribed in accordance with the data sheet is 30% (*P*^1^=.30), and that this efficacy will be greater if the maintenance regimen is extended over time. In this sense, it is hypothesized that the intermediate maintenance regimen could achieve an efficacy of 45% (*P*^2^=.40) and with the longest regimen, 50% sustained abstinence could be achieved (*P*^3^=.50). To obtain 80% power (pow=0.80) to detect differences at a 5% significance level (α=.05), 110 patients would need to be included in each arm. A loss rate of 21% is assumed, giving a final sample size of 402 patients (N=402).

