### Ethical Considerations

The trial will be conducted in accordance with the requirements documented in the latest version of the Declaration of Helsinki (Helsinki, 2024) and with the Standards of Good Clinical Practice. The trial is authorized for conduct by the Galician (Spain) Committee on Ethics in Medicines Research with code 2025/043 and by the Spanish Agency for Medicines and Medical Devices. It also has the agreement of the participating centers. This trial has been registered in the European Clinical Trials Register under EUDRACT code 2024-518936-36-00.

The researchers at each center will provide each participant with a patient information sheet, approved by the clinical research ethics committee, informing them about relevant study data and requesting access to their clinical and personal data recorded in their medical history and disclosed during visits. Permission is also requested for tests, examinations, and questionnaires, and the patient is informed that these actions are part of their daily clinical practice. In addition, the researcher will verbally inform the patient about the trial and answer their questions to ensure they understand the implications of their participation. The patient will be informed of their right to withdraw consent at any time and their right to have their data deleted. The patient will be informed of the possibility of being withdrawn from the study for safety reasons (an adverse event caused by the study medication) or for failure to comply with established procedures.

No patient may be included who has not given written informed consent to participate in the trial. Secondary analyses using existing data are included in the primary consent and do not require additional consent.

The research team and the sponsor of this study expressly undertake not to disclose the identity of the patients treated and to respect the confidentiality rules regarding the data and information to which they have access by participating in the trial.

In order to guarantee the confidentiality of the trial data, only the sponsor and members of the research team, the Research Ethics Committee for Medicinal Products, and the relevant health authorities will have access to them.

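### Efficacy is tied to an undefined evaluable population, with no all-randomised set: abstinence may be overstated, and the comparison is biased if loss differs by arm

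*Protocol article*

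**What the plan says.** Under Population of Analysis, the protocol article has a single sentence: "Efficacy and safety studies shall be conducted in the entire clinically evaluable population". Neither that section nor any other says who is evaluable. No intention-to-treat or all-randomised set is named, and there is no rule for a patient whose smoking status is unknown at 6 or 12 months.

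Three other places bear on the point:

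- **Sample Size Determination.** It first states that "110 patients would need to be included in each arm", then adds: "A loss rate of 21% is assumed, giving a final sample size of 402 patients (N=402".
- **Efficacy Analysis.** The outcome is a yes/no variable produced by an algorithm that will be built only after all study data are in. The effect measure is the relative risk.
- **Who leaves treatment or the study.** Criteria for Discontinuation of Treatment/Intervention says: "A patient will be withdrawn from the study when the investigator becomes aware that a participant is experiencing a serious or intolerable adverse event". The same section says "Noncompliance is not grounds for discontinuing treatment", and keeps a participant who becomes pregnant in the study after drug is stopped. Ethical Considerations says patients are told they may be withdrawn from the study for safety reasons or "for failure to comply with established procedures".

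**The concern.** This is a randomised, open-label superiority trial whose tested factor is treatment length. A set defined by what happens after randomisation no longer compares the groups as randomised. The wording is a stated choice that binds the efficacy analysis, so it is not simply a detail left for a later document.

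Whether a patient becomes evaluable could depend on the arm. The abstract says the longer regimen may threaten adherence. Adverse-event withdrawal removes the patient from the study, and drug exposure differs by arm from day 26. The arm that loses more of its continuing smokers would look better for that reason alone. The rates themselves also matter, because they feed the number needed to treat and the economic evaluation. As the outcome algorithm is to be built after open-label data are in, any later handling of lost patients would be chosen with the data in view.

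**Working it through.** **1. Reproducing the plan's figures.** An overall three-group chi-square test (2 df) with rates 30/45/50%, α = 0.05 and power 0.80 needs 109 per arm, against the stated 110. (The article gives the middle rate as 45% in words and .40 in brackets; .40 gives 116. I use 45% below.) Loss: 110 × 1.21 = 133.1, rounded up to 134; 134 × 3 = 402. The 21% is thus added on top of the number needed for analysis, which makes sense only if lost patients contribute nothing to it.

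**2. How many patients.** 402 × 0.21 = 84.4, so about 84 are lost. 402 × 0.79 = 317.6, or about 106 per arm.

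**3. Effect on rates at equal loss.** Let p be the true rate among all randomised, d the loss, and q the abstinence among lost patients. The evaluable rate is (p − q·d)/(1 − d). The documents give no q, so I show a range for p = 0.30, d = 0.21:

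- q = 0 (all lost patients smoke): 0.30/0.79 = 38.0%
- q = 0.15: (0.30 − 0.0315)/0.79 = 34.0%
- q = 0.30 (loss unrelated to outcome): 30.0%

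At q = 0 in every arm, 45% shows as 0.45/0.79 = 57.0% and 50% as 0.50/0.79 = 63.3%. The 50-day difference from control grows from 15 points to 0.15/0.79 = 19.0 points, so the number needed to treat moves from 1/0.15 = 6.7 to 1/0.190 = 5.3. The relative risk stays at 0.45/0.30 = 1.50, because 1 − d cancels.

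**4. Effect on the comparison when loss differs.** Assumptions: true rate 30% in both arms, 134 per arm, all lost patients smoke, two-sided 5% comparison of two proportions (the article does not state sidedness). The loss splits are illustrative; each averages 21%. The apparent relative risk is (1 − d_control)/(1 − d_extended). Rejection rates come from 200,000 simulated trials per row.

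| Loss, control v extended | Evaluable rates | Apparent RR | Rejection, evaluable | Rejection, all randomised, missing = smoking |
|---|---|---|---|---|
| 21% v 21% | 38.0% v 38.0% | 1.00 | 5.0% | 5.0% |
| 19% v 23% | 37.0% v 39.0% | 1.05 | 6.0% | 5.0% |
| 16% v 26% | 35.7% v 40.5% | 1.14 | 11.2% | 5.0% |
| 11% v 31% | 33.7% v 43.5% | 1.29 | 30.9% | 5.0% |
| 26% v 16% | 40.5% v 35.7% | 0.88 | 11.3% | 5.0% |

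The last row shows the bias running against the longer regimen.

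**5. Power at equal 21% loss, pairwise, two-sided 5%.** Evaluable analysis at 106 per arm, against all randomised at 134 with missing counted as smoking:

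- Planning rates read as evaluable rates: 62% to 57% (30 v 45%) and 85% to 80% (30 v 50%).
- Planning rates read as all-randomised rates: 79% to 72% and 96% to 92%.

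**The case against.** **The exclusion is inferred.** The article never says that lost patients are dropped. The term is undefined, and the later algorithm could count them as smoking. This stands as a limit on the wording. It does not rescue the plan, because the loss allowance points to exclusion and a rule set after the data are in gives no protection.

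**The size rests on assumptions.** That lost patients smoke, and that loss differs by arm, are not figures in the documents. This stands. Dosing is the same in all arms to day 25, all arms share one visit calendar, and the adherence remark is about tablets rather than visits. The only discontinuation figure quoted is 2.9% for adverse events, from a cited trial of 6- and 12-week courses. A 10- or 20-point gap in loss is therefore a what-if, and at 19% v 23% the effect is small.

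**Stronger readings the documents do not support.** A reader might infer that the evaluable set favours the longer regimens. It does so only if they lose more smokers, and the bias reverses if control does. A reader might see a plain contradiction on noncompliance. One passage concerns stopping treatment and the other leaving the study, in a summary of what patients are told; the wording needs reconciling but does not directly conflict. A reader might also expect more power from 134 rather than 106 analysed per arm. Under the proposed rule the added patients all count as failures, and power falls.

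**The article is condensed.** Imputation details and exact set definitions commonly sit elsewhere. That is fair, but the article does not stay silent: it names one set and applies it to efficacy.

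**Conclusion.** The point holds in this form: the only stated efficacy population is an undefined post-randomisation subset, and about 21% of patients would apparently fall outside it. If all lost patients smoke, 30% is reported as 38%; if some are abstinent the overstatement is smaller, and it vanishes if loss is unrelated to outcome. Equal loss with the same outcome pattern leaves the relative risk and the 5% error rate intact. Under the extreme assumption in step 4, unequal loss raises false rejection from 5% to about 6%, 11% or 31% as the gap widens from 4 to 10 to 20 points, in whichever direction the loss runs. The documents do not show that such a gap will occur. It should be corrected all the same, because it governs the primary comparison and the article's Results section reports only 12 preselected patients, none of whom had yet begun the initial visit.

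**What to change.** - Make the primary efficacy set all randomised patients, analysed in the arm assigned, with missing or unverified status at the endpoint counted as smoking. Fix this rule, and the outcome algorithm that contains it, before any data are seen.
- Define the evaluable set and keep it as a sensitivity analysis. Add one sensitivity analysis with a different missing-data assumption, since counting missing as smoking can itself mislead if lost patients are not all smokers and loss differs by arm.
- Reconcile the wording of Criteria for Discontinuation and Ethical Considerations on who leaves treatment and who leaves the study, because this determines who has outcome data.
- Restate the planning rates and the loss allowance in Sample Size Determination on the all-randomised basis.

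**Cost.** This is mainly wording, plus a revised sample-size paragraph. Reported abstinence will be lower in every arm that has losses, and power at equal loss is about 4 to 7 points lower.

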#### Analysis of Demographic and Baseline Characteristics

Demographic and baseline characteristics are summarized for each study group using descriptive statistics. For continuous variables, data on the number of observations, mean, SD, minimum and maximum, or median and IQR will be presented, depending on the fit of the variable to a normal distribution. Discrete variables will be presented with frequency and percentage. Appropriate inference tests chosen according to the nature of the variables were performed to compare these characteristics between the groups under study.

### Efficacy Analysis

To determine the main objective of the work, the efficacy variable will be constructed as a dichotomous variable, resulting from an algorithm that will be constructed for this purpose once all the data from the study have been obtained. To study the causality between efficacy and treatment prolongation, a multivariate logistic regression will be constructed. To determine candidate variables, candidate variables will first be tested in a univariate regression. Those variables whose statistical significance has a *P* value of <.20 will become part of a multivariate model. The model that best explains causality will be determined using a measure of relative statistical model quality, the Akaike information criterion. The risk measure to be calculated is the relative risk with its 95% CI. Interim follow-up assessments will be analyzed using a survival analysis to determine the duration of abstinence after the smoking cessation date.

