### Objectives

The overall objective of this study is to evaluate the efficacy, safety, and economic impact of 2 extended cytisinicline regimens (50 and 75 days duration) and compare them with the standard regimen (25 days).

The primary objective is to determine the efficacy of the maintained cytisinicline regimens (50 and 75 days) versus the standard 25-day regimen.

The secondary objectives are (1) to determine the percentage and number of adverse effects in each of the 3 treatment arms and (2) to analyze the economic impact of the maintained regimens versus the standard regimen in terms of cost-effectiveness and cost-utility.

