### Patient Enrollment and Randomization

All participants who consent to participate and who meet the eligibility criteria will be included in the trial and randomized. They are recorded in the data collection booklet designed specifically for this purpose.

Randomization will be performed in 2 phases. First, using a simple randomization procedure, participants are assigned to 1 of the 3 arms in a ratio of 1:1:1 (This is already mentioned in Study design).

Then, as noncompetitive recruitment is proposed, the sites are randomized (1 to 8, unrestricted) so that randomization determines where to start distributing the randomized sequence in the first phase. A randomization list will be generated using SAS 9 software (SAS Institute Inc) for Windows. This process will be carried out at the coordinating center, and each participating center will be provided with its own list according to the number of patients allocated. The aim is to achieve a balanced randomization in the treatment groups in the overall sample. There are no blinding techniques, as this is an open-label study. Blind-breaking procedures are therefore not applicable.

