### Specific Outcomes Efficacy

Different outcomes will be used to measure the efficacy of cytisine in each arm of the clinical trial.

The sustained abstinence rate will be determined in each of the three treatment arms at 6 and 12 months, based on carbon monoxide co-oximetry results in ppm. The correlation between the sustained abstinence rate in each of the three arms studied at 6 and 12 months, based on co-oximetry results, and the self-reported abstinence at 6 and 12 months will be calculated.

Additionally, point abstinence will be analyzed every 7 days in each of the 3 arms studied, based on the results obtained in the CO tests.

The percentage increase in abstinence rates will be compared with the increase in the duration of cytisinicline use. The number needed to quit smoking for one patient in each treatment group will also be calculated.

Interval abstinence will also be determined in this clinical trial. The abstinence rate will be analyzed from Day 25 to Day 50 in all 3 study groups and from Day 25 to Day 75 in all 3 study arms. The abstinence rate will also be determined from Day 25 (usual arm), Day 50 (extended arm 1), and Day 75 (extended arm 2) up to 6 and 12 months.

Relapse rates will be analyzed in each treatment arm. The frequency and percentage of relapses will be determined in those who quit smoking from Day 25 (usual arm), Day 50 (extended arm 1), and Day 75 (extended arm 2) up to 6 and 12 months in all 3 arms.

Craving and withdrawal symptoms will be assessed during the clinical trial. The mean Minnesota Nicotine Withdrawal Scale (MNWS) score and the mean craving score will be calculated at the initial in-person visit in all 3 arms, and their change from this visit will be measured on days 25, 50, and 75 in all 3 study arms.

Predictors of continued abstinence at 6 and 12 months of treatment and of relapse (clinical, anthropometric, demographic, and smoking-related variables) will be determined in all study arms.

Quality of life in each group will be calculated using the EQ-5D-5L scale score at baseline, 50 days, 90 days, 6 months, and 1 year.

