Other qualities of the smoker, such as the degree of motivation and self-efficacy, will be evaluated by the Analogue Visual Scale. This scale numerically identifies a smoker’s level of motivation and self-efficacy to quit smoking. A score above 7 indicates high motivation and self-efficacy to quit smoking [27].

The EQ-5D scale will be used in this clinical trial to assess the quality of life of smokers and its changes during the smoking cessation process. This scale measures the health status of smokers using 5 dimensions, including mobility, self-care, activities of daily living, pain and discomfort, and anxiety and depression. Participants score from 0 to 100 in each domain [31].

The urge to smoke in this study will be analyzed using the Craving Rate Score. This scale assesses anxiety or intense desire to smoke at baseline and during follow-up. It is scored from 0 to 4 [32].

The additional tests that will be performed on smokers participating in this trial include electrocardiogram, carbon monoxide levels, complete blood count, and a biochemical profile that includes liver enzymes, electrolytes, and renal function tests. Co-oximetry allows for the objective identification of smoking status, as well as confirmation of abstinence at each participant visit. A participant is identified as a nonsmoker when their CO levels measured by co-oximetry are below 10 ppm (Textbox 2).

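### The primary yes/no abstinence variable is to be defined by an algorithm written after all data are in, in an open-label trial, leaving time point, start of window and verification rule open

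*Protocol article*

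**What the plan says.** The article gives the primary objective only in general terms: "The primary objective is to determine the efficacy of the maintained cytisinicline regimens (50 and 75 days) versus the standard 25-day regimen". It names no measure and no time point.

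The Efficacy Analysis section makes the deciding variable a yes/no one for the main objective and states how it will arise: "resulting from an algorithm that will be constructed for this purpose once all the data from the study have been obtained".

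The other sections bear on that variable as follows.

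- **Specific Outcomes Efficacy:** "The sustained abstinence rate will be determined in each of the three treatment arms at 6 and 12 months". The same section lists further measures: "point abstinence will be analyzed every 7 days in each of the 3 arms studied"; abstinence over Day 25-50 and Day 25-75 in all three arms; and a set, running to both the 6- and the 12-month point, whose start differs by arm: "The abstinence rate will also be determined from Day 25 (usual arm), Day 50 (extended arm 1), and Day 75 (extended arm 2". None is called primary.
- **Textbox 2 (efficacy and safety variables):** lists continuous abstinence at six months and has no 12-month item.
- **Sample Size Determination:** speaks of sustained abstinence without a time point.
- **Data Collection Variables:** fixes one component: "A participant is identified as a nonsmoker when their CO levels measured by co-oximetry are below 10 ppm".
- **Patient Enrollment and Randomization:** "There are no blinding techniques, as this is an open-label study".

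**The concern.** The protocol is not silent here, leaving a detail to an analysis plan. It states when the rule will be made, and that time is after every outcome is known. An analysis plan that fixed the rule earlier would contradict the article. Nothing in the article says that whoever writes the algorithm will be kept from the allocation.

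The trial is meant to show superiority of the longer regimens. If the definition of success may be chosen with results by arm in view, the nominal 5% level no longer describes the chance of a false claim, and no later analysis can restore it. The choices left open are not cosmetic: 6 and 12 months can disagree, and so can windows that start on different days.

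**Working it through.** **1. Is the definition fixed anywhere?** Setting the sections side by side:

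| Component | Fixed? | Where |
|---|---|---|
| Family: sustained or continuous abstinence | In effect yes | Specific Outcomes Efficacy, Textbox 2, Sample Size Determination |
| CO threshold, below 10 ppm | Yes | Data Collection Variables |
| Time point | No: 6 and 12 months in one list, six months only in another | Specific Outcomes Efficacy; Textbox 2 |
| Start of the window | No | none |
| How CO and self-report combine into yes/no | No: Limitations says that they are combined, not how | Limitations |

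**2. The plan's own figure.** The stated 110 per arm is reproduced by a global three-group chi-square test (2 df, level 0.05) at rates 0.30, 0.45 and 0.50:

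- mean rate p̄ = 0.4167; Σ(pᵢ − p̄)² = 0.02167; p̄(1 − p̄) = 0.2431
- noncentrality λ = n × 0.02167 / 0.2431 = 0.0891n
- n = 109 gives power 0.804; n = 110 gives λ = 9.81 and power 0.807
- losses: 110 × 1.21 = 133.1, rounded up to 134; 134 × 3 = 402

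This figure does not depend on the time point, so it does not settle which one is meant.

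**3. What a free choice between 6 and 12 months does.** Let r be the correlation between the 6- and 12-month test statistics. The documents do not give it, so 0.7 to 0.8 is assumed. The two contrasts share a control arm at 1:1:1 allocation, so they correlate at 0.5. The false-positive rate is the chance, with no true difference, that any statistic exceeds 1.96 in absolute value, found by simulating correlated normal variables.

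| Situation | One fixed endpoint | Choice, r = 0.8 | Choice, r = 0.7 | Choice, r = 0.95 |
|---|---|---|---|---|
| One contrast | 0.050 | 0.078 | 0.083 | 0.065 |
| Two unadjusted contrasts | 0.091 | 0.139 | 0.149 | 0.116 |
| Global three-group test | 0.050 | 0.079 | 0.084 | 0.065 |

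At r = 0.7 to 0.8 the open choice adds about 3 points to one contrast or to the global test, and about 5 to 6 points to two contrasts.

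**4. Outcomes with arm-specific start days (a separate matter).** Taking 6 months as week 24, day 168, the follow-up is 168 − 25 = 143 days, 168 − 50 = 118 days and 168 − 75 = 93 days. The Introduction cites 20% relapse in the 2 months after treatment. Taken as a constant hazard, the same in all arms (an assumption), h = −ln(0.8)/60 = 0.00372 per day. Relapse to week 24 is then 1 − exp(−143h) = 41%, 1 − exp(−118h) = 36% and 1 − exp(−93h) = 29%, with no effect of treatment length. The exact figures depend on the constant hazard. With any positive hazard that runs equally in all arms from the start of each window, the shorter window shows less relapse.

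**5. Power if missing counts as smoking in all randomised patients.** Suppose the assumed rates apply to evaluable patients and 21% are lost. The rates become 0.79 × (0.30, 0.45, 0.50) = 0.237, 0.356, 0.395. With 134 per arm, λ = 134 × 0.01352 / 0.2208 = 8.21 and power is 0.73, against 0.81 at the planned 110 evaluable per arm. If the assumed rates already count losses as smokers, power at 134 per arm is 0.88.

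**The case against.** The best defence is that the endpoint is not really open. Sustained abstinence comes first in the abstract and in the efficacy outcomes, continuous abstinence at six months comes first in Textbox 2, and the sample size rests on sustained abstinence. The CO threshold is set, and Limitations says that CO is combined with self-report. The sentence could be a loose description of deriving a yes/no value from the visit data at the end. Much of this stands: the family of endpoint is clear. It does not close the matter. The text says that the algorithm itself will be constructed at that stage, and no section holds a definition that could merely be executed then.

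Three stronger readings may tempt a reader and are not supported.

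- **That the trial has no endpoint at all.** The family and the CO threshold are stated.
- **That the sentence alone takes the error from 5% to 14-15%.** About 9% already comes from testing two contrasts without adjustment, which is a different matter. If a single global test is primary, the figure is about 8%.
- **That the primary result will be biased by the Day 25/50/75 windows.** The article presents these as additional outcomes, alongside common-window versions, and nowhere places them in the primary algorithm.

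**Conclusion.** The point holds for the Efficacy Analysis sentence and what it leaves open: the choice of 6 or 12 months, the start of the window, and the rule joining CO and self-report. In an open-label superiority trial this needs correcting before outcomes are examined. For the 6- or 12-month choice alone, the cost is a rise from 5% to about 8% for one contrast, or from about 9% to 14-15% for two unadjusted contrasts, at an assumed correlation of 0.7 to 0.8. The need for the change rests on the wording and not on these figures.

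The arm-specific windows are a second, smaller matter about secondary outcomes. Their follow-up is unequal, and the relapse outcome is also restricted to those who had quit, a group formed after randomisation.

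**What to change.** Replace the sentence in Efficacy Analysis with a definition fixed before any outcome data are examined. It should name:

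- one primary endpoint, sustained abstinence, at one stated time point (for example 6 months, as in Textbox 2, with 12 months secondary);
- one start day common to all arms (for example day 5, the latest quit date that the article already sets for every arm);
- no smoking reported at each contact and CO below 10 ppm at each in-person visit;
- a stated missing-data rule.

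The sponsor may prefer another time point or start day; what matters is that it is fixed beforehand. For the abstinence and relapse outcomes that start at Day 25, 50 or 75 by arm, report within arm only. Base between-arm comparisons on a common window in all randomised patients.

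**Cost:** protocol wording and no new data. Table 3 already schedules a smoking statement at every visit and co-oximetry at every in-person visit. The Results section says that the preselected patients had not yet begun the initial visit at the time of writing. One consequence needs work: if missing is counted as smoking in all randomised patients, Population of Analysis, which now refers to clinically evaluable patients, must be aligned. The power must then be rechecked and restated: about 73% instead of 81% for the global test if the assumed rates apply to evaluable patients and 21% are lost.
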